## Abstract

**Background:**

There is a considerable body of evidence on the effectiveness of specific interventions in individuals who wish to quit smoking. However, there are no large-scale studies testing the whole range of interventions currently recommended for helping people to give up smoking; specifically those interventions that include motivational interviews for individuals who are not interested in quitting smoking in the immediate to short term. Furthermore, many of the published studies were undertaken in specialized units or by a small group of motivated primary care centres.

The objective of the study is to evaluate the effectiveness of a stepped smoking cessation intervention based on a trans-theoretical model of change, applied to an extensive group of Primary Care Centres (PCC).

**Methods/Design:**

Cluster randomised clinical trial. Unit of randomization: basic unit of care consisting of a family physician and a nurse, both of whom care for the same population (aprox. 2000 people). Intention to treat analysis.

Study population: Smokers (n = 3024) aged 14 to 75 years consulting for any reason to PCC and who provided written informed consent to participate in the trial.

Intervention: 6-month implementation of recommendations of a Clinical Practice Guideline which includes brief motivational interviews for smokers at the precontemplation – contemplation stage, brief intervention for smokers in preparation-action who do not want help, intensive intervention with pharmacotherapy for smokers in preparation-action who want help, and reinforcing intervention in the maintenance stage.

Control group: usual care.

Outcome measures: Self-reported abstinence confirmed by exhaled air carbon monoxide concentration of ≤ 10 parts per million. Points of assessment: end of intervention period and 1 and 2 years post-intervention; continuous abstinence rate for 1 year; change in smoking cessation stage; health status measured by SF-36.

**Discussion:**

The application of a stepped intervention based on the stages of a change model is possible under real and diverse clinical practice conditions, and improves the smoking cessation success rate in smokers, besides of their intention or not to give up smoking at baseline.

**Trial Registration:**

Clinical Trials.gov Identifier: NCT00125905

## Background

The data from the 50-year follow-up study involving British male doctors showed that one in two regular smokers of cigarettes die as a result of tobacco-related disease. The latest estimations showed that in Spain in 2001 there were 54,233 deaths attributable to tobacco consumption [1]. The data of the National Health Survey [*Encuesta Nacional de Salud*] of 2006 showed that 29,9% of the adult Spanish population smoked [2], with a clear tendency towards a decrease in males and an increase in females.

Primary care can play a key role in the control of tobacco consumption. The data from our country show that in many zones more than 75% of the population attend an outpatient consultation in the local Primary-Care Centre (PCC) at least once a year, and the average number of visits varies between 5 and 6 (data from the primary-care database of 2001; Sistema de Información de Atención Primaria, 2001). Spain has an almost universal coverage of the population by a public health system in which primary care is the first point of contact. This provides a unique opportunity for intervention, and therefore prevention, in a large number of subjects on many occasions even before chronic or severe diseases have begun. Furthermore, surveys as those cited above showed that more than 60% of smokers had a desire to quit smoking, and the majority of these individuals have at some time or other made an attempt to achieve this.

In the past few years, several national and international clinical practical guidelines have been developed with recommendations to intervene on the consumption of tobacco, based on help provided at health centers, both at primary and specialist care levels.

Since 1996, various clinical guidelines integrating all the evidence available from existing clinical research have been published in different countries. Most of them were from anglosaxon countries (mainly the USA, UK and Australia). For example, the guidelines from the US Public Health services published in 2000 (recently updated)[3] were based on approximately 6000 original articles and abstracts of congresses written in English and published between 1977 and 1999. More than 50 meta-analysis were carried out and became the basis for the recommendations developed by a panel of 18 experts. Following this, there was an external revision process by another group of 70 experts [4].

The guidelines from the United Kingdom originated from the meta-analysis derived from the American guidelines and from the Cochrane international collaboration reviews [5]. Furthermore, in the year 2000, appeared the First European Directives on the Treatment of Tobacco Dependence within the European Cooperative Project of the World Health Organization.

Some of the recommendations of these guidelines have been based on a large number of clinical trials and studies of intervention. However, in other cases, there has been weak evidence and the recommendations have been based on the consensus opinions of experts.

Examples of intervention from the primary-care perspective for which there has been grade A evidence (based on many high quality clinical trials containing consistent results) are:

• Primary health care teams should ensure that their records concerning which of their patients smoke are kept up to date [A]

• GPs should advise current smokers to stop during routine consultations at least once a year, offer a prescription for Nicotine Replacement Therapy (NRT), record the response to that advice, and arrange follow up where appropriate. [A]

• At the beginning of the study, and even now, the level of evidence for some key recommendation were still C and mostly derived from published guidelines (recommendations based on consensus). These include:

▪ The role of motivational interviewing in accelerating changes in the process of smoking cessation.

▪ The role of the primary care professionals in performing more intensive interventions.

▪ The role of primary care nurses in motivating and helping patients to quit smoking.

▪ The use in primary care of non-nicotine based pharmaceutical products such as bupropion, an atypical antidepressant considered in the guidelines as a first-line drug. At the start of this study there was only limited experience of its use in primary care.

There is only partial evidence for several of these recommendations. For example, in the case of motivational interviewing [6,7], the study by Butler et al showed outcomes less positive than those expected [8], and subsequent reviews showed some inconsistencies [9-12]. Motivational interviewing is difficult to evaluate because of its intrinsic nature (variability and adaptation to characteristics both from patients and health professionals, and from the interaction between them in each clinical encounter) and also due to the difficulty of finding useful and appropiate measures of success. Another important aspect to consider is the fact that motivational interviewing requires a change in the way health professionals interact with patients.

The Cochrane review of smoking cessation interventions conducted by nurses showed that there can lead to potential benefits and that there is fair evidence of their effectiveness. Again there are few studies in primary care and some of these studies show that the interventions carried out during preventive check-ups are less effective [13].

The use of bupropion was not yet protocolised in primary care, although the Cochrane review does recommend it as a first-line drug. [14].

One of the conceptual models that has been most extensively used to explain the process of change in addictive behaviour is that developed by Prochaska and DiClemente in 1982. These researchers defined a series of successive stages each of which require different types of interventions [15,16]. The use of this model is frequently linked to the motivational interviewing strategies described earlier. It is recommended that the interventions applied in primary care must be orientated towards achieving advances in this addiction process, and not only to giving up smoking. As such, stage change can be used as an intermediate measure of the effectiveness of the interventions. The majority of the clinical guidelines used in our Spanish environment include an assessment of the stage of smoking cessation in which the individual smoker is currently located [17].

Although the amount of research about smoking intervention is impressive, many of the studies have been conducted in highly selected populations of smokers and there have not been any studies that have evaluated all the range of interventions developed, applying them in a stepped manner to non-selected smokers who consult primary care centers for other reasons. Interventions include brief motivational interviews for smokers at the precontemplation – contemplation stage, brief intervention for smokers in preparation-action who do not want help, intensive intervention with pharmacotherapy for smokers in preparation-action who want help, and reinforcing intervention in the maintenance stage.

In Spain, the first studies date from the end of the 1980s when a group of primary care professionals in Barcelona (including two of the researchers of this study; [name] and [name]) replicated the effectiveness of the brief intervention study of Russell et al in the UK in 1979 [18,19].

Since then, and extending their field of study to include the primary care environment, the same research team have evaluated the effectiveness of nicotine chewing gum and nurse-based advice [20]. Subsequent studies by Quilez, Salvador, Comas, Torrecilla, etc. [21-24] have found results consistent with those of the international studies. Some of these studies had also been carried out in primary care centers, but by health-care professionals specially trained in this area.

Among the published studies there are at least two types of interventions which have been widely evaluated: the Doctors Helping Smokers (DHS) Program proposed by Solberg [25,26], adapted to Spain by Solberg and Nebot and applied in Spain by [name], [name], [name] and [name] (members of the ISTAPS research group) and the Program to Quit Tobacco by Grandes and Cortada [27]. The DHS program is based on the proposals of the first guidelines of American National Cancer Institute at the end of the 1980s which are easily applied in primary care. The main limitations of the program arose from the very brief intervention proposed and from the lack of a formal evaluation of its effectiveness in Spain. [28].

The study by Grandes et al. is a quasi-experimental study which included a large number of smokers with an evidence-based strategy. However, it does not include current recommended strategies such as motivational interviewing, more intensive help (the authors evaluated a therapeutic plan with three visits and one telephone call), nor the use of other drugs (other substitutes for nicotine than patches and bupropion) [29].

Hence, when faced with reviewing the evidence and developing a clinical guideline for Spain, the authors of the present project found that there was no clear evidence either for some of the proposed recommendations, or for the overall strategy. This led to the current proposition for a study identifying this evidence. In order to put into practice the intervention proposed health professionals must be trained. Some parts of the intervention (those related with motivational interviewing) require not only the development of skills but also a change in the way health professionals interact with patients. For this reason, and in order to minimize contamination, the unit of randomization and analysis was the basic care unit consisting of a physician and nurse who take care of the same list of patients, both of whom received a 20-hours training course at the beginning of the study.

The opportunity to detect and follow-up a cohort of persons from before quitting smoking to more than 1 years post-quitting would facilitate the study of variation in the overall health-related quality of life produced as a result of the process of quitting smoking, and also provide a measure of the impact on health status. The studies published about this theme are comparisons of the perceptions of health-related quality of life in smokers and ex-smokers [30]. Serial data in clinically relevant moments of the smoking cessation process would highlight the times and the scale at which the most relevant changes in the health-related quality of life are produced.

The SF-36 is a multi-purpose, short-form health survey validated in Spain by Alonso et al [31]. It consists of 36 questions measured in an ordinal scale. It can be self-administered or used in personal or telephone interviews. This yields a profile of functional health and well-being score, as well as psychometrically-based physical and mental health summary measures The profile considers 8 scales: Physical Functioning, Role-Physical, Bodily Pain, General Health, Vitality, Social Functioning, Role-Emotional, Mental Health and two summary measures: Physical Component Summary (PCS) and Mental Component Summary (MCS).

Additionally, one of the items evaluates the change in health status over the previous year. The items detect not only positive but also negative health status. The SF-36 is sufficiently sensitive to changes when compared to other questionnaires such as the Nothingham or the Sickness Impact Profile that have been especially useful in clinical trials up until now. One version of the SF36 that measures the health perception over the precedent week, known as the acute version, enables the changes to be evaluated within the interval of time envisaged in the present study.

## Objectives

### Objectives

• To evaluate the effectiveness of a stepped smoking cessation intervention based on a transtheoretical model of change that uses the pharmacological and non-pharmacological methods proposed by evidence based Clinical Practice Guidelines for smoking cessation in primary care centres. The effectiveness will be measured at patient level as the continuous abstinence for at least one year, adjusting for the effect of cluster randomization.

• To assess the health-related quality of life change in relation to the smoking cessation process.

## Methods/design

### Study design

Cluster randomized clinical trial

### Setting

Primary Care Centers (PCC).

### Study population

All the basic care units of health professionals belonging to the Spanish Preventive Services and Health Promotion Research Network (redIAPP) that expressed their intention to participate were included (n = 121). These health professionals worked in 82 primary care centres in 11 different regions of Spain.

Between the years 2003 and 2004, individuals aged between 14 and 75 years old who attended the primay care center for any reason, who answered positively to the question "Do you smoke?" and who provided informed consent to participation in the present study, were recruited. People suffering from terminal illnesses, severe psychiatric disorders, addiction to other psychoactive substances, or those unwilling to participate in the study were excluded. The recruitement continued for 12 months.

Unit of Randomization: Basic care unit. The system of randomization was centralized and computer generated.

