### Sample size calculation

Based on different assumptions

• Power 80%, alpha 0.05, potential study withdrawal (15%).

• A difference of 5% between the success rate of the intervention (10%) and control group (5%) -> a sample size of 499 in every group was needed.

• A difference of 20% between the success rate of the intervention (30%) and control group (10%) for people in the preparation stage -> a sample size of 110 in the preparation stage in every group was needed. Previous studies in Spain (Grandes et al. 2001) showed that approximately 16% of smokers seen in primary care centres were in the preparation stage, and thus, it was necessary to include 687 smokers in every group to obtain 110 in the preparation stage. As this number is greater than the 499 stated previously, this number is used for input in adjusting for the design effect.

• It was considered feasible that each basic care unit would include some 25 individuals in the study.

• The intracluster correlation coefficients (ICC) for outcome variables in cluster randomization clinical trials on guidelines implementation strategies in primary care are generally below 0,05 [32]. This ICC translates into a cluster size of 25 in a design effect of 2.2.

As such, the definitive sample size for the study would be 3024 patients (1512 in each group) corresponding to 121 basic health-care units (61 in each group, intervention and control).

The sample size calculations were performed with the Granmo program (version 5.2).

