## Discussion

The present study evaluates, under near real conditions, the effectiveness in primary care of an overall strategy of smoking cessation, that includes specific interventions addressed to people in all the stages-of-change. It is one of the biggest studies ever undertaken, not only in primary care but at all levels of clinical services. Given the almost universal coverage of primary care in Spain, and considering that many people in the country belongs to social class III to V, it is expected that the majority of the participants of the study will belong to these social classes, generating evidence of effectiveness in this type of population.

Another strength of the study is the large number of health-care professionals and patients who are involved, reinforcing the external validity of the data.

The theoretical framework used is the stages-of-change model of Prochaska and Di Clemente. Despite the fact that some authors such as West [33] or Riensma [12] have questioned the utility of the model in the past years, it remains as one of the most used conceptual frameworks. Since one of the criticism made of the studies using the model is the use of only one of the constructs (the stages of change), in our study we make use of all of them: stages, processes, self-efficacy and decisional balance; we also validate our Spanish version in a complementary study. Health-care professionals who volunteered to participate in the present study could have been more motivated than the health-care professionals working in other PCCs. If this were to be the case, any resulting bias would be in the direction of more conservative estimates of the effects of the intervention. It has been decided to randomize basic care unit instead of smokers as it would be very difficult for a health-care professional (particularly one who is well trained in applying a specific anti-smoking intervention) to withhold this intervention in accordance with the randomization procedure for specific individuals; this would be especially true in the case of the patient having certain pathologies related with smoking or those who had tried to quit many times before, etc. Given the feasibility of recruiting a considerable number of basic care units in control and intervention groups, we believe that this type of cluster randomized assignment is necessary and we hope this will result in comparable groups of basic care unit (health professionals) and patients.

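### Each unit enrols about 25 of some 310 to 450 eligible smokers after allocation, with no stated selection rule, so randomising units does not ensure comparable patients

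*Protocol article*

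**What the plan says.** - **Allocation and training.** Study population says that basic care units were randomised by a central, computer-generated system. Only the intervention professionals take the course (Description of the intervention). The Background says of a unit's physician and nurse: "both of whom received a 20-hours training course at the beginning of the study".
- **Recruitment.** Patients were recruited in 2003-2004 over 12 months. The entry criterion in Study population is "individuals aged between 14 and 75 years old who attended the primay care center for any reason, who answered positively to the question" on smoking, plus consent and a short list of exclusions. No order or sampling of approach is given.
- **Number per unit.** Sample size calculation: "It was considered feasible that each basic care unit would include some 25 individuals in the study".
- **Start of treatment.** Intervention patients are treated in the 6 months after their own inclusion, so a unit treats early patients while it recruits later ones.
- **Blinding.** Unit staff administer the clinical part of the questionnaire. Only the telephone interviewers are described as blinded (Data collection).
- **Analysis.** Statistical analysis plans a baseline comparison of the groups and a multilevel model with a random intercept for cluster. The only covariate it names is the baseline value of the dependent variable.
- **Comparability.** The Discussion argues for cluster allocation and adds: "we hope this will result in comparable groups of basic care unit (health professionals) and patients".

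**The concern.** Randomising units balances the units, and with them the smokers on their lists. It does not balance the patients whom each unit later picks from its list. If a unit takes a small part of its eligible smokers, and those who choose know the arm, the two arms can choose differently. A professional newly trained to help people quit might approach those who seem ready to quit, while a control professional might approach smokers more evenly. The article does not say that this happened, but nothing in its text prevents it.

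Readiness at entry predicts quitting: the plan's own control rates are 10% in the preparation stage and 5% overall. A readier intervention arm would therefore show more abstinence with no effect of the intervention, and the primary comparison would be biased in its favour. The Discussion considers only that volunteer professionals may be more motivated, and treats that bias as conservative. It does not mention selection after allocation, which could act in the opposite direction.

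**Working it through.** **1. The plan's own figure.** Design effect: 1 + (25 - 1) x 0.05 = 2.2. Preparation-stage requirement: 110 / 0.16 = 687.5 per group. Then 687 x 2.2 = 1511.4 and 687.5 x 2.2 = 1512.5, which agrees with 1512 per group and 3024 in total. 3024 / 25 = 120.96, or 121 units. Twenty-five patients per unit is therefore the working figure of the design.

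**2. Eligible smokers per unit in 12 months.** Inputs:
- list size: "both of whom care for the same population (aprox. 2000 people" (Abstract)
- yearly attendance: "more than 75% of the population attend an outpatient consultation in the local Primary-Care Centre (PCC) at least once a year" (Background)
- smoking prevalence: "showed that 29,9% of the adult Spanish population smoked" (Background)

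2000 x 0.75 x 0.299 = 448.5, and 25 / 448.5 = 5.6%. The list may include people outside ages 14-75, and the article does not say how many. If 70% or 90% of the list is in range (assumption), the pool is 314 or 404 and the fraction 8.0% or 6.2%. At 16% in preparation, 0.16 x 314 = 50 to 0.16 x 448.5 = 72 such smokers attend each unit, more than enough to fill 25 places. Exclusions and refusals would shrink the pool, but the article gives no figures for them.

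**3. Does the planned model correct for selection?** Everyone smokes at entry, so baseline abstinence has the same value for all and explains nothing. The random intercept allows for correlation within units, not for a difference between arms in who was enrolled. The baseline comparison could reveal an imbalance in stage, but no consequence is attached to it.

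**4. Size of a false difference with no treatment effect.** The plan's control rates are 5% overall and 10% in preparation, with 16% in preparation. The implied rate in the other stages is (5 - 0.16 x 10) / 0.84 = 4.05%. Hold the control arm at 5% and let the intervention arm enrol a share s in preparation. The false difference is (s - 0.16) x (10 - 4.05) points. For the last column, the effective size per arm after 15% withdrawal and the design effect is 1512 x 0.85 / 2.2 = 584, with a two-sided normal test at 5%.

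| Share s (assumed) | Intervention rate | False difference | Part of planned 5 points | Type I error |
|---|---|---|---|---|
| 16% | 5.00% | 0 | 0 | 5% |
| 21% | 5.30% | 0.30 | 6% | about 6% |
| 26% | 5.60% | 0.60 | 12% | about 7% |
| 32% | 5.95% | 0.95 | 19% | about 11% |

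As an example, for s = 32% the standard error is sqrt((0.0595 x 0.9405 + 0.05 x 0.95) / 584) = 0.0133. The shift is 0.0095 / 0.0133 = 0.72 standard errors, and the chance of passing 1.96 in either direction is about 11%.

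**The case against.** **The article may simply be silent.** It condenses a fuller protocol, and its time-line and algorithm (Figures 1 and 2) are not shown. A selection rule, or the order of randomisation and inclusion, may stand there. The article does not say when units were randomised relative to recruitment, or who took consent. This stands as a limit: knowledge of the arm and enrolment by unit staff are inferences. They are strong ones, because one arm is trained at the start, treatment follows each inclusion, and the sample size section has each unit including its own patients.

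**Everyone was asked.** Step 1 of the intervention says that all people accessing the centre were asked about tobacco. That describes the intervention, not recruitment in both arms, and it does not explain how some 25 were enrolled from several hundred.

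**The check is already planned.** Statistical analysis includes a baseline comparison, and stage and Richmond score are collected. This stands, and it lowers the weight of the point. What is missing is a correction in the primary model.

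Four stronger readings are tempting, but the documents do not support them:
- *That the arms did recruit differently.* Nothing shows this. The design leaves the route open and no more.
- *That the false difference is larger.* The planned intervention rates are 30% in preparation and, by the same arithmetic, (10 - 0.16 x 30) / 0.84 = 6.19% elsewhere. With these, shares of 21% and 26% give 11.2% and 12.4%, or apparent differences of 6.2 and 7.4 points. Those figures assume the full treatment effect. With no effect, the same shifts give 0.3 and 0.6 points.
- *That the preparation-stage comparison is biased by the same mechanism.* It holds stage fixed, so a change in stage mix alters its numbers, not its contrast.
- *That the article claims an unselected sample.* The Background phrase "applying them in a stepped manner to non-selected smokers who consult primary care centers for other reasons" describes what earlier studies had not done.

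**Conclusion.** The point holds as a weakness of design and analysis. About 25 of roughly 310 to 450 eligible attending smokers per unit (5.6-8.0%) enter after allocation. The article states no selection rule, and the recruiters very probably know their arm. Comparability of patients is hoped for rather than ensured, and the named covariate cannot restore it for abstinence.

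The likely size is modest. Under the plan's control rates, the false difference is about 0.3 points for a 5-point rise in the preparation share and about 1 point if the share doubles. That would not by itself produce the planned 5 points, but it bears on the primary comparison and could raise the type I error to about 11% in the doubled case. These figures rest on assumed shifts in one measured factor; selection on other aspects of motivation is not counted. The point should be fixed, but it does not invalidate the trial.

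**What to change.** **For patients already recruited** (the article places recruitment in 2003-2004):
- Add stage of change, Richmond score and Fagerström score at entry as covariates in the primary multilevel model for abstinence, specified before the outcome is compared by arm. Data collection lists all three, so no new data are needed. Report the result without these covariates beside it.
- Present the planned baseline comparison of these variables by arm as an explicit check for recruitment bias.
- State in the Discussion that patients were selected after allocation, very probably by professionals who knew their arm, and that this could favour the intervention. If the full protocol holds a selection rule, or the figures show a different order of events, say so there.

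This costs a few lines of text and three covariates. Adjustment deals only with selection that these variables capture.

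**Where recruitment is still open, or in a later trial of this design:** offer the study to consecutive eligible smokers in both arms from a fixed start date until 25 are included. Keep a short log of everyone asked (age, sex, stage, consented or not). The cost is some clinic time and possibly slower enrolment.
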